#### Qualitative analysis

Open-text responses from questionnaires will be analysed using conventional content analysis, following the approach described by Hsieh and Shannon, to inductively identify and categorise recurring themes, barriers, facilitators and explanatory factors relevant to implementation and patient experience.^60^ Findings will be summarised descriptively and illustrated with representative quotations.

#### Mixed methods data integration

Quantitative and qualitative data will be collected concurrently and analysed separately. Integration will occur during the interpretation phase using joint display tables, in which qualitative findings will be used to contextualise and explain quantitative results (eg, reasons underlying tracer preferences). Joint display tables will align quantitative outcomes with illustrative qualitative data, enabling contextualisation and explanatory comparison. This approach follows established mixed-methods integration principles described by Fetters *et al.*^61^

### Patient and public involvement

Patients were actively involved throughout the design and conduct of this trial. A dedicated patient panel was established in collaboration with Stichting Buddyhuis, a Dutch peer-support organisation that matches patients with breast cancer with current or former patients.^62^ The patient panel comprises four women with lived experience of SLNB using ^99m^Tc-nanocolloid and/or ICG. As integral and equal members of the project team, the patient panel participated in a focus group using the Value Proposition Canvas to identify patients’ needs regarding SLNB and explore the perceived added value of ICG-guided SLNB.

The patient panel also co-developed and pilot-tested the patient questionnaire and reviewed patient information materials and the informed consent documents to ensure clarity, relevance and acceptability. The patient panel will continue to contribute systematically throughout the trial via iterative evaluation cycles, including the interpretation of findings relevant to patient experience.

In addition, the Patient Advisory Group of the Dutch Breast Cancer Association (Borstkankervereniging Nederland) and the Dutch Breast Cancer Research Group (Borstkanker Onderzoek Groep), consisting of patient representatives, reviewed and endorsed the current study.

### Ethics and dissemination

This study is subject to the Dutch Medical Research Involving Human Subjects Act (Wet medisch-wetenschappelijk onderzoek met mensen, WMO). Ethical review and approval were obtained from the Medical research Ethics Committees United (MEC-U; Central Committee on Research Involving Human Subjects dossier number NL87551.100.24; approval date 6 November 2024). The study was prospectively registered at ClinicalTrials.gov (NCT07146295) and in the Dutch Trial Register (Landelijk Trial Register; LTR; NL-005321). The boards of directors of all participating hospitals approved local participation in the study.

Written informed consent will be obtained from all participating patients. Consent is required because the study involves prospective data collection for research purposes and because the tracer used for SLNB may differ from standard practice during the phased implementation. Patients will be informed about the study objectives, procedures, potential risks and benefits, data handling and their right to withdraw without consequences for their care.

The study is considered low risk. ICG has an established safety profile, is non-ionising and is widely used in clinical practice for other indications.^63^ Adverse events potentially related to ICG use will be monitored and recorded throughout the study. The trial will be conducted in accordance with the principles of the Declaration of Helsinki and Good Clinical Practice guidelines.

Study results will be disseminated through publication in open-access, peer-reviewed scientific journals and presentation at national and international conferences focusing on oncological surgery, breast cancer care and/or image-guided surgery. In addition, implementation products developed within the study, including a clinical protocol, implementation guide, educational materials and patient information resources, will be made publicly available to support national scale-up.

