#### Timeline and cluster transition

All participating hospitals commenced Phase I on 18 April 2025. The trial spans 18 months and is divided into six consecutive 3-month periods. Three clusters, each comprising two or three hospitals, transition sequentially from Phase I to Phase II at 3-month intervals.

Cluster transitions are not randomised but scheduled pragmatically based on site readiness, defined as the availability of ICG, access to a NIRF imaging system and completion of training. Although non-randomised transitions may reduce control over potential time-related confounding, the relatively short study duration and stable clinical context minimise the likelihood of major secular trends, making this approach appropriate for a pragmatic implementation study.

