### Sample size

A formal sample size calculation was not performed, as the INFINITE trial primarily aims to implement ICG-guided SLNB in routine clinical practice, while concurrently collecting real-world data on effectiveness. Moreover, sample size estimation for stepped-wedge cluster designs is inherently challenging due to the sequential rollout across clusters.^41^ Instead, the study uses a convenience sample of real-world data from seven purposefully selected hospitals.

The seven participating hospitals collectively perform approximately 1500 SLNBs via axillary incision annually. Over the planned study period, this corresponds to approximately 2250 SLNB procedures. Given the limited exclusion criteria and an anticipated exclusion rate of ≤10%, approximately 2025 patients are expected to be eligible. Based on practical feasibility and consent rates observed during the early study phase, approximately 850 patients are expected to be included. The estimate is informed by initial inclusion patterns and may vary modestly over time as site-specific workflow stabilises.

The anticipated sample size is considered sufficient to estimate key quantitative outcomes with acceptable precision. For the primary implementation outcome, penetration, an expected Phase III sample of approximately 280 SLNB procedures yields a 95% CI of roughly ±6 percentage points when the proportion is near 50%, with narrower intervals for lower or higher values, based on binomial approximation. For effectiveness outcomes, assuming a per-case SLN detection rate of approximately 95% in Phase III, the corresponding 95% CI would be approximately ±2–3 percentage points. This level of precision is appropriate for pragmatic hybrid effectiveness-implementation research, in which the aim is to describe real-world uptake and contextual variation rather than to formally test hypotheses.

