### Statistical analysis

#### Quantitative analysis

Baseline characteristics and quantitative outcome variables will be summarised using descriptive statistics. Continuous variables will be reported as means with SD or as median with IQR, based on distribution. Distributional assumptions will be assessed by visual inspection of histograms, and homogeneity of variances will be evaluated using Levene’s test. Dichotomous and categorical data will be presented as frequencies with percentages.

Where applicable, comparisons will be performed using the Student’s t-test for normally distributed continuous variables, the Mann-Whitney U-test for non-normally distributed continuous variables, and the χ^2^ or Fisher’s exact test for categorical variables.

Penetration, the primary implementation outcome, will be reported as a proportion with corresponding 95% CIs, without formal between-group comparisons. Adoption and fidelity outcomes will be reported descriptively as proportions with accompanying counts. Safety outcomes will be reported descriptively as proportions of patients experiencing ICG-related (serious) adverse events, with corresponding 95% CIs.

Effectiveness outcomes will be analysed according to study phase. A pre–post implementation analysis will compare observational cohorts of Phase I (^99m^Tc-nanocolloid) and Phase III (ICG). For these phases, effectiveness outcomes will be reported with 95% CIs and include per-case SLN detection rates, per-node SLN detection by tracer, number of excised LNs per procedure, detection time, SLNB duration and pathological outcomes of excised SLNs. Phase II will be analysed separately using a within-patient approach. In this phase, per-node SLN detection will be reported separately for ICG and ^99m^Tc-nanocolloid, and tracer concordance will be evaluated by quantifying agreement at the LN level. In addition, a paired within-patient comparison of per-case SLN identification by ICG versus ^99m^Tc-nanocolloid will be performed. Phase II outcomes will be reported descriptively with corresponding 95% CIs, using paired statistical methods where appropriate.

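### The Phase I versus Phase III effectiveness comparison names only unadjusted tests, although both cohorts are consent-gated, non-randomised and expected to hold about 42% of eligible patients

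*Protocol article*

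**What the plan says.** All references are to the protocol article.

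- **Allocation.** Under Study design, Phase I uses 99mTc-nanocolloid as standard care and Phase III uses ICG alone; both are called observational cohorts. Timeline and cluster transition states: "Cluster transitions are not randomised but scheduled pragmatically based on site readiness".
- **Consent.** Study population lists lack of consent among the exclusions. Ethics and dissemination requires written consent from every participant and gives two reasons: prospective data are collected for research, and consent is needed "because the tracer used for SLNB may differ from standard practice during the phased implementation".
- **Inclusion.** Sample size expects that "approximately 2025 patients are expected to be eligible" and that "approximately 850 patients are expected to be included". The second figure is based on feasibility and on consent rates seen early in the study.
- **Analysis.** Under Quantitative analysis, a pre–post analysis "will compare observational cohorts of Phase I" with Phase III on detection, excised nodes, times and pathology, reported with 95% CIs. The comparison methods named are the t-test, Mann-Whitney, chi-square and Fisher tests, two-sided, with p<0.05 as significant. Data collection records demographic and clinical variables for each patient; Quantitative analysis only summarises them.
- **Limitations.** Timeline and cluster transition and Strengths and limitations discuss time trends, and the latter also learning effects. Neither mentions selective inclusion.

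**The concern.** The intended tracer follows from the hospital and an openly scheduled phase, and a patient enters the analysis only after consenting. In Phase I the first reason for consent is the only one that applies, since care is unchanged. In Phase III both can apply. The process that decides who is approached and who agrees may therefore differ between the two cohorts being compared, and more than half of eligible patients are expected to remain outside.

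If patients who are harder to map, or who have more extensive disease, enter one phase less often than the other, the contrast mixes case mix with tracer. This could happen within a single hospital over a short time, so the article's argument from short duration and stable context does not answer it. The results are meant to describe real-world effectiveness and to inform guideline consideration, so the contrast will be read as being about the tracer.

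**Working it through.** **1. Recruitment chain (Sample size; Timeline and cluster transition).** "The seven participating hospitals collectively perform approximately 1500 SLNBs via axillary incision annually" and "The trial spans 18 months and is divided into six consecutive 3-month periods".

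- Procedures: 1500 × 18/12 = 2250, as stated.
- Eligible at 10% exclusion: 2250 × 0.90 = 2025, as stated.
- Included share: 850/2025 = 42.0%; not included: 2025 − 850 = 1175.
- The stated exclusion rate is an upper limit. At 5% or 0% excluded the share is 850/2137.5 = 39.8% or 850/2250 = 37.8%, so 42% is the highest value these figures allow.
- The 10% allowance cannot include non-consent, so eligible here means before consent.

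**2. Per phase.** Take the first transition at month 3, the others at 3-month steps, a 6-month Phase II and equal volume per hospital (assumptions). With clusters of 2, 3 and 2 hospitals:

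- Phase I: 2×3 + 3×6 + 2×9 = 42 hospital-months
- Phase II: 7×6 = 42
- Phase III: 2×9 + 3×6 + 2×3 = 42

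Each phase holds one third: 2025/3 = 675 eligible and 850/3 = 283 included, in line with the article's figure of about 280 for Phase III.

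**3. Stated precision.** Half-width = 1.96 × √(p(1−p)/n), n = 280:

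- p = 0.50: 5.9 points (article: about 6)
- p = 0.95: 2.6 points (article: 2–3)

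These describe one cohort. For the Phase I versus III difference at 95% with 280 per phase: 1.96 × √(2 × 0.95 × 0.05/280) = 3.6 points.

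**4. Illustration of selective inclusion.** Assume true detection of 95% in both phases and no selection in Phase I. Let r be the inclusion rate of would-be failures in Phase III relative to that of successes. Observed Phase III detection = 0.95/(0.95 + 0.05r).

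| r | Observed Phase III | Spurious gain (points) | Chance of p<0.05 |
|---|---|---|---|
| 1 | 95.0% | 0 | about 5% (nominal) |
| 0.8 | 0.95/0.990 = 96.0% | 1.0 | about 8% |
| 0.5 | 0.95/0.975 = 97.4% | 2.4 | about 33% |

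The last column is the normal-approximation power of a two-sided 5% test of two proportions with 280 per phase. The values of r are not taken from the documents.

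**5. Why few patients matter.** At 95%, 280 procedures give 0.05 × 280 = 14 expected failures, so the estimate is sensitive to the inclusion or loss of a handful of patients.

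**The case against.** The strongest reply has five parts.

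- **The 42% does not show differential selection.** It comes from feasibility and early consent rates. All hospitals began in Phase I, so those rates arose wholly or largely before ICG-only use. Equal non-inclusion in both phases would limit generalisability without, by itself, biasing the contrast. This stands: 42% is an inclusion rate that shows room for selection, not its presence.
- **Two links are inferences.** A reader might infer that each patient's tracer is known before consent, and that consent has a documented different meaning in each phase. The article states neither. It gives its reasons for consent for the study as a whole and one set of eligibility criteria for all phases. Implementation outcomes also allows delayed adoption and relapse, so the phase sets the intended tracer only. This stands, and limits the point to a possibility.
- **The illustration is hypothetical.** Even the 2.4-point shift lies inside the ±3.6-point half-width of the difference, and Sample size says the aim is descriptive. This mostly stands, although the article does set a significance threshold and a shifted estimate misleads without a test.
- **An analysis plan, not shown, may add adjustment.** It may. But the article names specific unadjusted tests for a non-randomised contrast, so this concerns a stated choice rather than missing detail.
- **Phase II compares tracers within patients.** Correct. That comparison is untouched by differences in inclusion between phases, so the evidence on detection does not rest on Phase I versus III alone.

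**Conclusion.** The point holds as a weakness in the stated analysis. Two non-randomised, consent-gated cohorts, with about 42% of eligible patients expected across the study, are to be compared with unadjusted two-sample tests although patient characteristics are recorded. The article's discussion of validity covers time trends and learning but not who is included.

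A reader might go further and conclude that the comparison is biased, or that it favours ICG. The documents do not support that: they give no inclusion rate by phase, so neither direction nor size can be derived. The spurious gains of 1.0 and 2.4 points rest on assumed values of r, on true detection of 95% in both phases, and on no selection in Phase I. They show that modest differential inclusion could matter beside a ±3.6-point half-width, not that it will occur.

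**What to change.** 1. **Quantitative analysis.** Make the main Phase I versus III effectiveness estimates adjusted for named patient characteristics from those recorded under Data collection, with the list fixed before Phase III data are viewed. Use standardisation or propensity weighting for detection, because failures are few. Keep the unadjusted results as secondary.
2. **Included fraction.** Report it by hospital and phase, using the aggregated procedure counts already needed for penetration. These are counts rather than a patient list, so they support fractions but not a comparison of included with non-included patients. Where fractions differ between Phases I and III, add a simple sensitivity analysis of how many failures among non-included patients would change the conclusion.
3. **Strengths and limitations.** Add selective inclusion, and state that the comparison applies to consenting patients.

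The cost is wording and modest extra analysis. The article describes the recorded variables only in general terms, so their adequacy for adjustment should be confirmed when the list is fixed. Intervals will be slightly wider and model-dependent. Adjustment will not remove selection on unmeasured factors, such as a surgeon's expectation of poor mapping, which is why the second and third steps are needed as well. The Phase II analysis needs no change.

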## Discussion

### Clinical impact

Fluorescence-guided SLNB using ICG offers a promising alternative to radioisotope-based techniques that may reduce patient burden, logistical complexity and healthcare costs. Despite growing evidence supporting its clinical performance and advantages over traditional tracers, uptake of ICG-guided SLNB in routine practice remains limited. This appears to reflect implementation-related challenges rather than uncertainty regarding clinical effectiveness. The INFINITE trial is designed to address this implementation gap by prospectively evaluating how ICG-guided SLNB is introduced, adopted and embedded in routine care, alongside assessment of real-world effectiveness, patient-reported experience and costs.

By embedding implementation and effectiveness evaluation within a structured, phased implementation strategy, the study aims to generate clinically relevant data that reflect variation in institutional context, surgical teams and learning curves. The inclusion of per-case and per-node effectiveness outcomes, temporal performance measures and pathological findings allows assessment of SLNB performance under real-world conditions. Implementation outcomes such as penetration and adoption describe the extent to which ICG-guided SLNB is taken up in routine practice, while measures of fidelity, appropriateness, feasibility and acceptability provide insight into why implementation succeeds or lags across sites. This integrated approach is intended to support clinicians, hospital administrators and guideline developers in making informed decisions regarding broader adoption and sustainable integration of ICG-guided SLNB.

### Strengths and limitations

The major strength of the INFINITE trial lies in its design. The hybrid effectiveness-implementation approach enables concurrent evaluation of implementation and clinical outcomes during real-world adoption. The stepped-wedge cluster design supports phased rollout, maintains transitional safety and provides repeated opportunities to evaluate and refine implementation strategies over time. The fixed transition period with dual-tracer use supports surgeon training and enables within-patient comparisons, which may strengthen confidence in diagnostic reliability during early adoption. The multicentre setting further increases generalisability by capturing variation in institutional context, geographical location and surgical volumes.

An additional strength is the use of an integrated, theory-informed implementation approach that combines a process model (Grol and Wensing), a determinant framework (CFIR) and an evaluation framework (Proctor *et al*).^48^,^50^ This allows the trial not only to measure implementation outcomes but also to systematically identify barriers and facilitators, inform the adaptation of implementation strategies and interpret observed variation in uptake and performance across sites. Embedding this approach within iterative evaluation cycles is designed to support learning during implementation while generating transferable insights for future scale-up.

Several limitations should be acknowledged. Cluster transitions are based on site readiness rather than random allocation. Although reflecting real-world implementation, a non-randomised comparison between pre- and post-implementation phases may be influenced by temporal trends or learning effects within the study period. Yet, the relatively short trial duration and stable clinical context limit the likelihood that such trends materially affect this comparison. The questionnaire-based implementation outcomes (appropriateness, feasibility and acceptability) are formally assessed at a single time point in Phase III. This timing was chosen so that providers can accumulate sufficient experience to give an informed appraisal, but it may limit characterisation of how these outcomes evolve during implementation. Some implementation outcomes, such as fidelity, rely on surgeon self-reporting and may be subject to reporting bias. The sample size is determined by feasibility rather than formal power calculations, which may limit precision for selected secondary outcomes. Although the study includes in-hospital data and collects patient-incurred costs, it is not designed to provide a full societal cost-effectiveness analysis.

Finally, the trial is also conducted in an evolving axillary management landscape, in which recent and ongoing trials suggest that axillary de-escalation, including omission of SLNB, may be safe in selected patients.^64^,^67^ However, this evidence base remains limited, and uptake in routine practice is cautious. SLNB remains indicated for many patients, underscoring the continued need for safe, efficient and consistently implemented techniques.
